
**Fig. 2 Fig2:**
[figure not shown]
Expected sample sizes in all four study arms

### Data collection and management

Primary and secondary outcomes, as well as patient characteristics, are extracted from claims-data at the health insurer involved, CareCockpit data and primary data from a patient survey.

Claims-based data are collected for a time frame starting 6 months before baseline until 3 months after the intervention phase. Data from the CareCockpit is transferred along with administrative data each quarter year.

For the conduction of the patient survey, GP-practices are informed in advance on when to conduct the survey and they receive all material needed including the patient questionnaires, the sealed box to collect them, and detailed information on how to conduct the survey in the practice. The patients are asked in the practice by their physician after discharge to take part in the survey by filling in the questionnaire in the practice. Questionnaires will be handed out to all eligible patients per practice and time point in both intervention and control practices. The sealed boxes with filled-in questionnaires will be sent by mail using an enclosed post-paid box directly to the aQua-Institute.

The hospitals have the choice to either integrate the questionnaire into their hospital information system as an electronic questionnaire (transfer to the aQua-Institute via secure file transfer protocol (SFTP)-servers) or to fill in paper-based questionnaires that are sent to the aQua-Institute via mail using enclosed post-paid envelopes. If GP-practices are responsible for determining the HOSPITAL Score, the items of the HOSPITAL Score are part of the assessment for planning of follow-up care within the CareCockpit and will be transferred to the evaluating institutions along with other CareCockpit data. All data necessary to determine the score can be extracted from the discharge letter.

As the intervention is implemented in a pragmatic study design, differences in quality between the GP-practices and hospitals can occur. For quality assurance purposes, all GP-practices are therefore continuously being contacted via telephone by the study central office. Within the phone calls, recruitment status in the GP-practice is being checked and support with the implementation is offered. Additionally, any issues that occur with the implementation will be addressed in feedback meetings. Furthermore, the CareCockpit software guides through the assessments.

### Data analysis

The outcome evaluation is divided into a primary analysis and secondary analyses. Design and analysis of the claims-data based evaluation will closely follow a recently published US-study on reduction of rehospitalisations in high-risk patients [2]. They are well-grounded and established in the literature on programme evaluation, especially in econometrics and quantitative social science, and increasingly in health systems research [21–24].

#### Primary analysis

In the primary analysis, a difference-in-difference model is applied [21, 25, 26]. The change of the primary outcome (before vs. after the intervention) of each intervention group will be pairwise compared to the control group. Put in a simple way, the following model will be estimated:$$ {\mathrm{rehospitalisation}}_{\mathrm{t},\mathrm{i}}={\upbeta}_0+{\upbeta}_{\mathrm{T}}\mathrm{x}\ {\mathrm{t}\mathrm{ime}}_{\mathrm{t},\mathrm{i}}+\kern0.37em {\upbeta}_{\mathrm{I}}\mathrm{x}\ {\mathrm{i}\mathrm{ntervention}}_{\mathrm{i}}+\kern0.37em {\upbeta}_{\mathrm{I}\mathrm{x}\mathrm{T}}\mathrm{x}\ {\left(\mathrm{intervention}:\mathrm{time}\right)}_{\mathrm{t},\mathrm{i}}. $$

The index t describes the point in time, i is the index for the considered observation. The following parameters will be estimated:β_0_: interceptβ_T_: effect of time; the general change from before to after the interventionβ_I_: difference between groups at baselineβ_IxT_: difference between the change (before and after comparison) in the control and in the intervention group; the main parameter for the outcome evaluation

The assumptions of this model are sufficiently discussed in the literature. The parameter β_IxT_ is the main parameter to evaluate the effectiveness of the intervention, describing the difference in changes between the two groups over time.

The above model is adjusted for the covariate service level of the hospital and the location (general allocation to districts). Other covariates will be already considered during the matching procedure when generating the control group.

The primary outcome is binary. Thus, logistic regression models will be applied. Furthermore, there is a hierarchical structure underlying the data, with cases nested in patients, and patients nested in practices or hospitals, respectively. This structure is considered in the model by including random intercepts at each level. The combination of random and fixed effects results in a mixed logistic regression model. A compound symmetry correlation structure will be assumed when fitting the models.

In the primary analysis, one model per intervention arm will be applied which leads to the need of an adjustment of our testing procedure for multiple testing. In order to meet the global level of significance of 5%, the following procedure will be applied: Study arm 1 (planned admission into a participating hospital) is expected to show the strongest effect. Therefore, this comparison will be considered using the full α-level of 5%. If the null hypothesis of no intervention effect can be rejected, the second study arm is tested at the same level. In a last step, the study arms 3 and 4 are tested simultaneously by splitting the level of significance equally according to Bonferroni to 2.5% each.

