### Study population / eligibility criteria

GP-practices within the intervention region have to participate in GP-centred care (*Hausarztzentrierte Versorgung/* HzV). GP-centred care is a programme where, amongst others, the GP has a gate-keeping function (further description of the programme provided by Wensing et al. [13]. Furthermore, Gp-practices have to employ a Care Assistant in General Practice (*Versorgungsassistentin in der Hausarztpraxis/* VERAH). Inclusion criteria for patients are age of 18 years and older, ability to give consent, insurance with the sickness fund AOK Baden-Wurttemberg, participation in GP-centred care according to § 73b SGB V, and at least one hospitalization during the intervention phase. Patients residing in long-term care facilities are excluded from study participation.

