### Control group

Using propensity score matching a control group from non-participating HzV-GP-practices in non-participating districts is built. Using claims-based data, age, gender, practice size and length of enrolment in GP-centred care and the district are considered to build the control group on practice level; to build a patient control group, age, gender, indication group and Charlson Comorbidity Index are used. Patients in the control group are not participating in the study and do not receive any intervention components.

The control group for the patient survey comprises patients that from approx. 50 comparable HzV-practices outside the intervention region. The inclusion criteria of the intervention group apply for patients of the control group.

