### Outcomes

The primary outcome is the number of rehospitalisations due to the same indication (three-digit ICD-10-GM code) within a time frame of 3 months (90 days) to the outpatient sector. This outcome is collected from claims-data on a case level, meaning that each patient can have more than one rehospitalisation, whereof all are considered in the analyses.

The following indicators have been defined as secondary outcomes and are based on pseudonymised claims-data, data collected within the CareCockpit software in GP-practices as well as patient survey data:number of rehospitalisations due to the same indication (three-digit ICD-10-GM code) within a time frame of 30 daysnumber of hospitalisations due to ambulatory care-sensitive conditions [17]number of patients discharged to the outpatient sector from a participating hospital where the prescription of medication is delayed [18]number of patients discharged to the outpatient sector from a participating hospital where referral to other health practitioner/s (*Heilmittel*) is delayednumber of patients discharged to the outpatient sector from a participating hospital where prescription for medical products/devices (*Hilfsmittel*) is delayednumber of patients discharged from a participating hospital who use emergency or rescue services (emergency medical service (*Ärztlicher Bereitschaftsdienst*), emergency ambulance (Notarztwagen), ambulance emergency response vehicle (*Notarzteinsatzfahrzeug*), ambulance, rescue helicopter (*Primärtransport – Luft*) within a time frame of 3 monthsaverage care cost per year and patient participating in the VESPEERA programmepatient-reported experiences and health-related outcome of cross-sectoral care using the German version of the instrument Patients’ Experiences Across Health Care Sectors (PEACS) [16]health-related quality of life, using the instrument EuroQol (EQ-5D) [19].

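### The primary model leaves age, gender, indication group and Charlson index to the matching, which is not shown to balance before-period and after-period cases separately

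*Protocol article*

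**What the plan says.** The Control group section describes how controls are found: "Using propensity score matching a control group from non-participating HzV-GP-practices in non-participating districts is built". At practice level it uses age, gender, practice size, length of enrolment in GP-centred care and district. At patient level, "to build a patient control group, age, gender, indication group and Charlson Comorbidity Index are used". All of these come from claims data.

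The Primary analysis section then sets the contrast: "The change of the primary outcome (before vs. after the intervention) of each intervention group will be pairwise compared to the control group". On covariates it says "The above model is adjusted for the covariate service level of the hospital and the location (general allocation to districts"), followed by "Other covariates will be already considered during the matching procedure when generating the control group". Matching is thus the stated reason for leaving the other variables out of the model.

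Three further statements bear on this. The outcome is counted per hospital case (Outcomes: "This outcome is collected from claims-data on a case level"). Patients qualify through "at least one hospitalization during the intervention phase" (Study population / eligibility criteria). The before period rests on earlier claims (Data collection and management: "Claims-based data are collected for a time frame starting 6 months before baseline until 3 months after the intervention phase").

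Neither Secondary analysis and sensitivity analysis nor Analysis sets brings the omitted covariates back.

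**The concern.** Matching on a covariate and adjusting for it do different jobs here. A match makes two groups of patients alike at the time the covariates are measured. The primary parameter compares how the rehospitalisation rate of cases changes over time in two groups. A patient may contribute several cases, or none, to either period, and indication and comorbidity can differ from one admission to the next. Balance between patients therefore does not guarantee balance in each of the four group-by-period cells.

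A differential shift has a plausible source. Intervention patients are identified by their practice and give consent around an admission in the intervention phase (Recruitment). Controls do not take part and are found in claims data. The arms are split by planned and unplanned admission (Table 1), but admission type is not among the listed patient matching variables. Indication is likely to be prognostic, because the outcome is readmission for the same three-digit diagnosis.

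The stated rationale is also applied unevenly. District is used in the practice-level match and location by district is modelled as well. If matching on district does not rule out adjusting for it, the same holds for the other variables.

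A spurious interaction in arm 1 would reach further than that arm, since rejection there opens the test of arm 2.

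**Working it through.** **1. The plan's own yardstick.** Sample size calculation states that 1905 cases in arm 1, with an equal matched control group, can show a fall from 23% to about 15% with 80% power at 5%.
- Without clustering, 23% against 15% needs about 377 per group (two-sided), so 1905 cases imply a design effect of 1905/377 = 5.05.
- The stated inputs give 1 + 0.6 × 0.3 = 1.18 for 1.6 cases per patient at ICC 0.3, and 1 + 539 × 0.03 = 17.17 for 540 patients per hospital at ICC 0.03.
- The product is 20.26, the effective size is 1905/20.26 = 94 per group, and the detectable reduction is about 14.7 points.

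The stated 8 points are therefore not reproduced. That is a separate question. Here 8 points serves only as the plan's own measure of a relevant effect.

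**2. What omission does to the interaction.** Let γ be the log-odds effect per SD of a composite risk score (age, gender, indication, comorbidity), and let m be the mean score in each cell. If the score is left out, the interaction absorbs approximately

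γ × [(m intervention, after − m intervention, before) − (m control, after − m control, before)].

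A stable difference between groups cancels, and so does a shift common to both groups. Only a differential shift s remains, with bias of about γ × s on the log-odds scale.

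**3. Size.** The documents give neither γ nor s. Assumed ranges: γ from 0.3 to 0.8, s from 0.1 to 0.3 SD. Near a rate of 23%, points ≈ γ × s × 0.23 × 0.77 = γ × s × 0.177.
- Lowest: 0.3 × 0.1 × 0.177 = 0.0053, or 0.5 points.
- Highest: 0.8 × 0.3 × 0.177 = 0.0425. Averaging over the distribution of the score instead of using the linear approximation gives 4.0 points.

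Values averaged over the score, in percentage points:

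| γ per SD | s = 0.1 | s = 0.2 | s = 0.3 |
|---|---|---|---|
| 0.3 | 0.5 | 1.1 | 1.6 |
| 0.5 | 0.9 | 1.7 | 2.6 |
| 0.8 | 1.3 | 2.7 | 4.0 |

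Against 8 points this is 0.5/8 = 6% to 4.0/8 = 50%. A shift towards sicker cases in the intervention group hides a benefit. A shift the other way mimics one.

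**4. Simulation check.** Logistic difference-in-difference model, true interaction zero, 1905 cases in each of the four cells (the before-period numbers are assumed equal), mean rate 23%, 300 runs per setting, no clustering.

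| | Score omitted | Score in model |
|---|---|---|
| No differential shift: rejection at nominal 5% | 4 to 6% | 5% |
| Shift 0.1 to 0.3 SD: interaction OR | 1.01 to 1.23 | 0.98 to 1.01 |
| Shift 0.1 to 0.3 SD: rejection at nominal 5% | 6 to 50% | 4 to 6% |

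The rejection rates illustrate the mechanism only. With clustering the standard errors would be larger and these rates would not carry over as they stand.

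**The case against.** The strongest reply is that matching followed by a sparse difference-in-difference model is an accepted approach, and that the group term already removes stable differences. Age and gender can hardly shift within the same patients. The planned time-series analysis over 12 monthly points gives a partial check on diverging trends. All of this stands, and it limits the point to robustness. The time-series analysis does not adjust for case mix, however, so it does not close the gap.

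A reader might infer that matching cannot balance the two periods. The documents do not support that. They do not say when the covariates are measured or whether cases are matched by period, and matching within each period is feasible. An article may leave such detail to the full plan. What the article does fix is that matching replaces adjustment.

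A reader might also infer a gain in precision, on the ground that case mix accounts for part of the between-hospital variance. That does not follow. The design effect with 540 patients per hospital belongs to a two-group comparison at one time. Where the same hospitals supply cases in both periods, stable hospital variance largely cancels from the interaction. No document says how much of that variance case mix explains.

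Finally, adjustment can do harm if it uses values that the programme has changed. Repeat admissions count as cases, so comorbidity or indication recorded at a later admission may already reflect the intervention. This objection is sound and shapes the fix.

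**Conclusion.** The point holds as a weakness in robustness. In a non-randomised comparison of cases, prognostic variables already in hand are kept out of the primary model for a reason that does not cover the parameter being tested. The possible distortion is about 0.5 to 4 percentage points under the assumed ranges (differential shift 0.1 to 0.3 SD, log-odds effect 0.3 to 0.8 per SD), and zero if case mix moves alike in both groups. The upper end needs both a strong composite effect and the largest shift. The documents do not show that such a shift will occur, so it would be wrong to say that the analysis is biased. The change is worth making because it costs little and, in the simulation, did no harm when there was no shift.

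**What to change.** In the primary mixed logistic model, add as fixed covariates age, gender, indication group and Charlson index, together with the practice-level matching variables practice size and length of enrolment in GP-centred care. Keep hospital service level and location as planned. State that each covariate is measured at or before the index admission, with the same look-back in both periods, and that values at repeat admissions which the intervention could have altered are not used.

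The cost is a few more model parameters and some analysis work. The variables are already drawn from claims data for the matching, and the protocol expects no missing values in those data, so no cases should be lost. One thing to check is the look-back. The claims window is stated to open 6 months before baseline, so the earliest before-period admissions have little history inside it. An equal look-back may need a short window or earlier claims.

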### Sample size calculation

Since large-scale implementation of the VESPEERA program in a geographical region was intended, the number of participating GPs and hospitals was not restricted. Based on the number of GP-practices who participate in HzV-Care and the number of GP-practices who participate in the PraCMan programme, a number of 115 GP-practices are expected to participate. An estimation of the patient sample size was made using claims-data and several assumptions for hospitalisation rates, rates for planned and unplanned admissions, rates of patients with a high risk of rehospitalisation as well as drop-out rates. Assumptions were made based on analyses of AOK claims-data. Admissions are expected to be planned and unplanned in 50% of the cases, respectively. 56% of planned admissions are made by a GP and therefore can be included in the VESPEERA programme. 40% of planned admissions are cases that are expected to be treated in a participating hospital department. After discharge, we calculated with a 20% drop-out rate for patients who are transferred into a nursing home, who pass away or who do not seek GP contact after discharge. 60% of discharged patients are expected to have a risk of rehospitalisation (HOSPITAL Score indicating an intermediate or high risk for rehospitalisation). Figure 2 gives an overview on the sample sizes in each study arm. Given the estimated sample size, we can estimate the effect size (based on the hospitalisation rates after the intervention) that can be detected. Based on claims-data different numbers of hospitalisations can be expected for each of the intervention groups. The alpha level is set to 5%. The following power considerations are based on chi square tests (to test for group differences) and adjusted for the hierarchical structure of the data. The implemented models in the primary analysis will most likely lead to even higher power values. However, we consider the hierarchical structure of the data with cases nested in patients nested in hospitals or practices, respectively. A relatively high ICC (0.3) can be expected when considering measurements within patients, however the number of cases per patient will be relatively small (approx. 1.6 cases per patient). The clustering by hospitals or practices is taken into account with an expected number of approx. 540 patients per hospital and a presumed ICC of 0.03, which is a realistic value in health services research [20]. Furthermore, we assume a rate of re-hospitalisations of 23% in the control group. With a power of 80%, the following reductions in each of the intervention groups can be shown: For study arm 1 a sample size of 1905 cases can be expected. Hereby, a reduction of approx. 8% (from 23% to approx. 15%) can be shown. The control group will be matched and, therefore, the sample size will be the same. For study arm 2 when compared to the control group, the same reduction is detectable, as the same number of cases can be expected as in study arm 1. In a last step, both the study arms 3 and 4 are compared to the control group using a level of significance of 2.5%. In study arm 3, we expect a sample size of 3266 and, thus, a reduction of approx. 7% (from 23 to 16%) can be shown. In study arm 4, a sample size of 4899 hospitalizations can be expected which allows to show a reduction of approx. 6% (from 23 to 17%).

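### The primary difference-in-difference model has random intercepts only, so its standard error is too small if hospital or practice effects shift between the two periods

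*Protocol article*

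**What the plan says.** All of this is in the Protocol article. The Primary analysis section fits a logistic difference-in-difference model with fixed effects for time, intervention and their product. The product term "is the main parameter to evaluate the effectiveness of the intervention, describing the difference in changes between the two groups over time". The hierarchy is described as cases and patients, "with cases nested in patients, and patients nested in practices or hospitals, respectively". It is handled as follows: "This structure is considered in the model by including random intercepts at each level". The section then adds: "A compound symmetry correlation structure will be assumed when fitting the models". Period is not a level, and no random time slope, cluster-by-period effect or robust variance is named.

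The multiplicity procedure tests arm 1 at the full 5%, then arm 2 at 5% if arm 1 is rejected, then arms 3 and 4 at 2.5% each. There is one model per arm.

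The Sample size calculation section bases its detectable reductions on chi-square tests between groups. It says of the models actually planned: "The implemented models in the primary analysis will most likely lead to even higher power values".

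**The concern.** A random intercept gives each hospital or practice one deviation, shared by both periods. In a before-after change that deviation cancels, so the only variance left for the interaction is at case level. This is right only if the correlation between a cluster's pre-period and post-period effects is 1. Below 1, each cluster also carries its own shift. That shift is common to all its cases in a period, but the model spreads it over the cases as if it were independent noise.

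The article itself gives a reason why hospitals might shift without any programme effect. The Background reports a duty on hospitals from 1 October 2017 to offer structured discharge planning. Data collection starts 6 months before baseline. If baseline is May 2018, when the intervention phase began, the pre-period opens around November 2017, about one month after that duty. Hospitals may have adapted to it at different speeds.

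At stake are the width of the primary confidence intervals and the global 5% level. If every later step is tested only after arm 1 is rejected, the familywise error under the global null equals arm 1's own error. Secondary endpoints use the same strategy.

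**Working it through.** **What the plan gives.** There is no figure to reproduce on this point: the article states neither a between-period correlation nor a power for the interaction. Its detectable reductions refer to a post-period comparison. They do not follow from the stated 540 patients per hospital and ICC 0.03: the stated 23% to 15% needs 377 cases per group without clustering, so 1905 implies a design effect of 1905/377 = 5.05, whereas 1 + 539 × 0.03 = 17.2. That is a separate matter and nothing below depends on it.

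**Inputs from the article.** ICC ρ = 0.03; 1905 cases in arm 1, 3266 in arm 3, 4899 in arm 4; matched control groups of equal size; 25 hospital departments and 115 practices; 6 pre-intervention months and a 17-month intervention phase; alpha as above.

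**Assumptions.** Between-period correlation of the cluster effect c = 1.0, 0.9, 0.8, 0.6. Cases are spread evenly over 25 departments or 115 practices per group. The pre:post case ratio is 6:17, with equal periods as an alternative. Tests are two-sided. One cluster level is treated at a time.

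**Formulas**, per cluster and in units of the outcome variance, with h = 1/m_post + 1/m_pre:

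- true variance of the change: 2ρ(1 − c) + (1 − ρ)h
- variance that the random-intercept model reports: (1 − ρc)h
- k = square root of (true / reported)
- type I error = 2[1 − Φ(z/k)], with z = 1.960 at 5% and 2.241 at 2.5%

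**Worked case, arm 1, 25 departments, 6:17, c = 0.8.** m_post = 1905/25 = 76.2; m_pre = 76.2 × 6/17 = 26.9; h = 0.0503. True variance = 0.0120 + 0.0488 = 0.0608. Reported variance = 0.976 × 0.0503 = 0.0491. k = 1.113. Type I error = 7.8%.

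Type I error (%) by the same formula:

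| Setting | nominal | c = 1.0 | 0.9 | 0.8 | 0.6 |
|---|---|---|---|---|---|
| Arm 1, 25 departments, 6:17 | 5 | 5.0 | 6.4 | 7.8 | 10.6 |
| Arm 1, 25 departments, equal periods | 5 | 5.0 | 7.7 | 10.5 | 15.7 |
| Arm 3, 25 departments, 6:17 | 2.5 | 2.5 | 4.1 | 5.9 | 9.7 |
| Arm 1, 115 practices, 6:17 | 5 | 5.0 | 5.3 | 5.5 | 6.1 |
| Arm 3, 115 practices, 6:17 | 2.5 | 2.5 | 2.8 | 3.1 | 3.8 |
| Arm 4, 115 practices, 6:17 | 2.5 | 2.5 | 3.0 | 3.5 | 4.6 |

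**Simulation check.** Mixed logistic models with a cluster intercept only were fitted to binary data at 23% with no interaction and equal periods (1000 runs per setting). With 25 clusters of 76 cases per period, type I error was 4.2, 8.9, 9.9 and 18.5% at c = 1, 0.9, 0.8 and 0.5. With 115 clusters of 17 cases it was 4.4, 5.8, 6.2 and 8.4%. At c = 0.8 with 25 clusters, the mean model standard error was 0.111 against a true 0.137. A t-test on cluster-level changes in log odds, which carries the cluster-by-period variance, stayed at 4.2-5.4% in every setting (4000 runs each).

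**The power remark.** The post-only contrast has per-cluster variance ρ + (1 − ρ)/m_post, which for arm 1 over 25 departments is 0.03 + 0.97/76.2 = 0.0427. The ratio of the interaction's true standard error to the post-only one is:

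- 25 departments, 6:17: 1.07 (c = 1) to 1.19 (c = 0.8)
- 25 departments, equal periods: 0.77 (c = 1) to 0.94 (c = 0.8)
- 115 practices, 6:17: about 1.6

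Power can therefore move either way.

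**The case against.** The strongest reply is that the defect is conditional. If cluster effects are stable, the planned model holds its level, and the article gives no correlation to show otherwise. This stands. A reader might infer that the 5% level is certainly broken, and the document does not support that.

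Second, a reader might multiply the stated 540 patients per hospital by 1.6 cases to get 864 cases per cluster, or pool arms 1 and 3 to get (1905 + 3266)/25 = 207, and arrive at far larger inflation. Neither fits a planned model. 864 × 25 = 21,600 exceeds the 11,975 cases of all four arms together (1905 + 1905 + 3266 + 4899), and the arms are modelled separately.

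Third, the intervention is not simply assigned to whole hospitals. Arms depend on point of enrolment and medical need, and arms 2 and 4 are by definition admissions to non-participating hospitals. The treated unit common to all arms is the practice, where the inflation is slight. This also stands and limits the material concern to hospital-level clustering. For arms 2 and 4 that clustering cannot be sized, because the number of hospitals is not given.

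Fourth, the remark under Data collection and management that "differences in quality between the GP-practices and hospitals can occur" is weak evidence. It speaks of a possibility, and uneven delivery of an ineffective programme creates no shift under the null. The October 2017 duty is the better argument.

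Finally, it may be said that such terms belong in a statistical analysis plan. That would hold if the article were silent. It instead fixes intercepts at each level and names compound symmetry.

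**Conclusion.** The point holds in conditional form. The stated model assumes perfectly stable hospital and practice effects without giving a reason. If they are not stable, the interaction's standard error is too small.

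For a correlation of 0.9 to 0.6, ICC 0.03 and a 6:17 case ratio, type I error is about 6-11% for arm 1 and 4-10% against 2.5% for arm 3, both over 25 departments. With equal periods, arm 1 rises to about 8-16%. Over 115 practices arm 1 stays at about 5.3-6.1%. These ranges rest on the assumed correlation, pre-period case number and even spread over clusters. The single-level calculation also ignores the patient level.

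The power remark is unsupported as it stands. A reader might infer that power must fall, for instance because 6 pre-months against 17 multiply the case-level variance by 1 + 17/6 = 3.8. That factor assumes cases accrue in proportion to months, and it leaves out the gain from cancelling stable cluster effects. Whether power rises or falls depends on cluster size, stability and pre-period case numbers, which the article does not give. The plan should be changed, but the defect does not by itself invalidate it.

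**What to change.** In the Primary analysis section, add random hospital-by-period and practice-by-period effects to each arm's model, with hospital and practice crossed where patients of one practice use several hospitals. Alternatively, keep the mean model and use cluster-robust standard errors with a small-sample correction. Make this the primary analysis and replace the compound symmetry sentence accordingly.

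In the Sample size calculation section, delete the sentence on higher power, or replace it with a power figure for the interaction that states the cluster numbers, pre-period case number and between-period correlation used.

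The cost is one more variance term per clustering level and somewhat wider confidence intervals; data collection does not change. If cluster effects are in fact stable, the added variance is estimated near zero and little is lost.

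### Holm's step-down in place of the fixed 2.5% Bonferroni split for arms 3 and 4 would gain power at the same familywise level; the entry condition for that step should be written down

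*Protocol article*

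**What the plan says.** The Protocol article, section Primary analysis, fits one model per intervention arm and sets out an ordered procedure for the four comparisons with the control group. Its aim is explicit: "In order to meet the global level of significance of 5%, the following procedure will be applied".

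- **Arm 1** is tested first, at the full 5%.
- **Arm 2** has a written condition: "If the null hypothesis of no intervention effect can be rejected, the second study arm is tested at the same level".
- **Arms 3 and 4** come in a last step, in which "the study arms 3 and 4 are tested simultaneously by splitting the level of significance equally according to Bonferroni to 2.5% each". No condition for entering this step is written.

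The section Sample size calculation uses the same level: "In a last step, both the study arms 3 and 4 are compared to the control group using a level of significance of 2.5" per cent, again with no entry condition. It gives the power behind the detectable effects: "With a power of 80%, the following reductions in each of the intervention groups can be shown".

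**The concern.** The split keeps each of arms 3 and 4 at 2.5% even after the other has been rejected. At that point the 2.5% spent on the rejected hypothesis can be passed to the remaining one without raising the familywise error. A p-value between 2.5% and 5% in one arm, beside a p-value below 2.5% in the other, would be declared non-significant although a 5% familywise level does not require it. These are the two largest arms, with 3266 and 4899 expected cases.

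The same sentence also leaves unsaid when the last step may be entered. The condition is written from arm 1 to arm 2 and then not repeated. If arm 1 or arm 2 missed significance, it would be open to argument whether a result in arm 3 or 4 counts as confirmatory.

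**Working it through.** **Inputs.** From Primary analysis: global level 5%; arms 1 and 2 at 5%; arms 3 and 4 at 2.5% each. From Sample size calculation: 80% power for each arm, at 2.5% for arms 3 and 4. Assumptions of mine: two-sided tests (sidedness is not stated), a normal approximation, and independent comparisons, with correlation 0.5 as a second case. The 80% is taken as stated and not re-derived here.

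**1. The plan's own 5%, with the last step gated on arms 1 and 2.**
- If arm 1 or arm 2 is a true null, a false rejection must first get through a test at 5%, so the error is at most 0.05.
- If arms 1 and 2 both work and arms 3 and 4 are null, Bonferroni gives at most 0.025 + 0.025 = 0.05.

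The stated 5% is therefore reproduced under this reading.

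**2. Holm under the same gate.**
- If arms 3 and 4 are both null, a first false rejection needs a p-value below 2.5%, so the bound is again 0.025 + 0.025 = 0.05.
- If only one is null, it is tested at 5% at most.

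Simulation (2,000,000 draws) agrees: no configuration exceeded 5.0%.

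**3. Power once the step is reached, independent tests.**
- The shift giving 80% power at two-sided 2.5% is 2.241 + 0.842 = 3.083.
- Power of the same test at 5% is Φ(3.083 − 1.960) = 0.869.
- Holm, one arm: 0.80 + (0.869 − 0.80) × 0.80 = 0.855.
- Holm, both arms: 0.869² − 0.069² = 0.751. Bonferroni, both arms: 0.80² = 0.64.
- At least one arm, either method: 1 − 0.20² = 0.96.

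| Last step reached | Bonferroni | Holm |
|---|---|---|
| Each arm, independent | 80.0% | 85.5% |
| Both arms, independent | 64% | 75% |
| At least one, independent | 96.0% | 96.0% |
| Each arm, correlation 0.5 | 80.0% | 84.6% |
| Both arms, correlation 0.5 | 68.7% | 77.9% |
| At least one, correlation 0.5 | 91.3% | 91.3% |

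**4. Overall chance per arm, including the gate.** If every arm has 80% power and the comparisons are independent, arms 1 and 2 are both passed with probability 0.80 × 0.80 = 0.64.
- Bonferroni: 0.64 × 0.80 = 0.512.
- Holm: 0.64 × 0.855 = 0.547.

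The gain is about 3.5 points. At correlation 0.5 the simulated figures are 61.1% and 63.7%.

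**5. If the last step were entered without the gate.**
- Ungated, all nulls true, independent: 1 − 0.95 × 0.975² = 0.0969. At correlation 0.5 the figure is 8.7%. The upper bound is 0.05 + 0.025 + 0.025 = 0.10.
- Gated on arm 1 only, arm 1 effective and the others null: the same expression applies, 9.7%.
- Ungated with Holm: also 9.7%. Holm does not stand in for the gate.

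**The case against.** **Bonferroni is not an error.** It is valid, prespecified and consistent with the 2.5% in the sample size section. That is right, and the point is about efficiency only. Bonferroni also gives simple simultaneous 97.5% intervals for the two arms, and Holm has no equally simple counterpart. This is a real but small cost. It bears on interval reporting and does not make Bonferroni better for the test decision.

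**The gain is smaller than the step-level figures suggest.** This also stands. The rise from 80% to 85.5% holds only after arms 1 and 2 have been rejected. Overall it is about 3.5 points per arm, and the chance of at least one success in the last step does not move.

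**A reader might infer that the plan tests arms 3 and 4 whatever happens in arm 2, and so breaches its global 5%.** The article does not support this. Nowhere does it say that the last step runs regardless. It describes ordered steps, writes the first gate, calls the final stage a last step and states the 5% aim. The natural fixed-sequence reading meets 5% exactly. The unwritten condition is an ambiguity, not a shown breach. The article is also condensed, and the full protocol or analysis plan, not shown here, may state the gate. The Bonferroni split, by contrast, is fixed in the text at hand.

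**Conclusion.** The point holds as an improvement to a stated rule. Holm at 5% in the last step keeps the familywise level and rejects everything that Bonferroni rejects, and sometimes more. Given that the step is reached, it adds about 5.5 points of power per arm and 11 points for showing both effects under independence (4.6 and 9.2 points at correlation 0.5). Overall it adds about 3.5 points per arm under independence (2.6 at correlation 0.5) if all four arms have 80% power. The fact that Holm never rejects less needs none of these assumptions; only the size of the gain does.

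The missing entry condition is secondary. With the likely intended gate the level is 5.0%. Figures of 9.7% (independence), 8.7% (correlation 0.5) and at most 10% arise only if the step is read as ungated, or, in the case shown, as gated on arm 1 alone.

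**What to change.** Replace the sentence on the last step in Primary analysis with, for example: *Arms 3 and 4 are tested only if the null hypotheses for arms 1 and 2 have both been rejected; within this step Holm's procedure at an overall 5% is used (smaller p-value against 2.5% and, if rejected, larger p-value against 5%).* Align the matching sentence in Sample size calculation. It may keep 2.5% for planning, since power under Holm is at least that under Bonferroni once the step is reached. It should add that the 80% for arms 3 and 4 is conditional on passing arms 1 and 2.

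The change should be fixed before outcome data are analysed. It costs a sentence in each section and no extra patients. If simultaneous intervals for arms 3 and 4 are wanted, the 97.5% Bonferroni intervals can still be reported, with a note that they may not match the Holm decision in every case. If the sponsor prefers to keep Bonferroni for that reason, the entry condition should still be written.
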